### Data Management and Analysis

Data management and statistical analysis conducted during the intervention will be entered into the research log book and checked by a statistician. All data will be encoded and accessible only to those allowed by [name] The local ethics committee has already approved the study and confirmed the detailed specifications on data security provided to them. The data will be later keyed into a computer using Microsoft Excel 2016 (Microsoft Corporation) and checked for input errors. Descriptive analyses will be conducted using mean, SD, median, IQR, and counts, based on distribution. To investigate the effects of the intervention, a comparison of the pre- and postintervention data will be conducted using the Wilcoxon signed-rank test for the indicators of the malaria. For group comparisons, the *t* test will be used to compare means, while the chi-square test will be used to compare the proportions of malaria home-based management indicators in the intervention and control groups. Differences will be considered statistically significant at a *P* value <.05. Missing data will be handled using the multiple imputation method.

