## Methods

### Study Area

This study will be community-based, occurring in 2 health areas of the West Region of Cameroon: the Fombap health area in Santchou Health District where the integrated CDI strategy will not be implemented (intervention group) and the Baneghang health area in Penka-Michel Health District where the integrated CDI strategy is being implemented (control group).

Figure 1 shows the multistage sampling approach, in which probability and nonprobability sampling methods were used to select the 2 health areas. 

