### Data Collection Procedure

Trained interviewers were blinded to group allocation and collected data using pretested questionnaires. For baseline data, a pretested questionnaire was administered to home caregivers on the perception (knowledge, attitudes, and practices) of malaria. This questionnaire will be repeated at the end of the intervention. During the intervention, a structured data collection form will be used and will contain monthly malaria follow-up indicators recorded by home caregivers in the intervention group and the malaria follow-up indicators recorded by CHWs in the control group. The data source for the study will be the malaria register used for the intervention in the Fombap health area and the malaria register used by the CHWs in the Baneghang health area.

In the experimental group (Fombap health area), 6 CHWs were chosen from the Fombap population of 5875 inhabitants, corresponding to 1 CHW per 1000 inhabitants. In each CHW’s zone, the CHW conducted a census of all the households where there is at least one child younger than 5 years and their home caregiver. From this census, children younger than 5 years old and their home caregivers were randomly selected for enrollment in the study. They will be trained in the prevention, diagnosis, and treatment of uncomplicated malaria at home. Malaria kits will be distributed to home caregivers to take care of the children younger than 5 years at home.

With Baneghang health area as the control group, 6 CHWs were also randomly selected from the 9 in the Baneghang health area. In each CHW’s zone, the CHW conducted a census in all the households where there is at least at least one child younger than 5 years and their home caregiver. After the households were identified, children younger than 5 years old and their home caregivers were randomly selected for enrollment in the study. Figure 2 shows the outline of the sampling method for the intervention.

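### The pre/post Wilcoxon test is assigned to malaria indicators for which no pre-intervention measurement is described, and a within-area change cannot test the between-strategy hypothesis

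*Protocol article*

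**What the plan says.** **Analysis.** The Data Management and Analysis section begins its inferential part with the effect of the intervention, for which it states that "a comparison of the pre- and postintervention data will be conducted using the Wilcoxon signed-rank test for the indicators of the malaria". The next sentence adds between-group tests: a t test for means and, for proportions, "the chi-square test will be used to compare the proportions of malaria home-based management indicators in the intervention and control groups". Significance is set at P<.05. No test is singled out as the one that decides the hypothesis. The Abstract names a further technique, one-way analysis of variance, for comparing the two strategies.

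**Data.** The Data Collection Procedure section describes one baseline instrument: "For baseline data, a pretested questionnaire was administered to home caregivers on the perception (knowledge, attitudes, and practices) of malaria". On its second use the section says: "This questionnaire will be repeated at the end of the intervention". The malaria indicators have a different timing: "During the intervention, a structured data collection form will be used and will contain monthly malaria follow-up indicators recorded by home caregivers". That describes Fombap; in Baneghang the CHWs record them. The sources are the register used for the intervention in Fombap and the CHW register in Baneghang.

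**Question.** The hypothesis at the end of the Introduction is that empowered home caregivers do better than CHWs under the integrated community-directed intervention (CDI). The primary outcome and the post-intervention evaluation (Step 6) also compare the two strategies.

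**The concern.** A signed-rank test needs a before value and an after value on the same unit. As the article describes the data, the malaria indicators have only the second. The sentence that carries the claim about the intervention's effect therefore cannot be carried out on the variables it names.

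Pairs do exist for the KAP questionnaire, but there a within-area change answers a question other than the stated hypothesis. Anything that moves over the study period moves the pre/post difference, whether or not one strategy is better than the other. Because no test is named as decisive, a significant within-area P value could be reported as the effect of the intervention while the comparison with CHWs shows nothing.

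**Working it through.** **1. What the trial was sized for.** Inputs from Sample Size Calculation: p1 = 0.44, p2 = 0.33, z values 1.96 and 0.842, stated n = 300 per group.

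- Pooled proportion: (0.44 + 0.33)/2 = 0.385.
- Pooled formula: 2 × 0.385 × 0.615 × (1.96 + 0.842)² / 0.11² = 307.3.
- Unpooled formula: (0.44 × 0.56 + 0.33 × 0.67) × 2.802² / 0.11² = 303.3.

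Both are within 3% of 300. The stated size is that of a two-sided comparison of two independent groups (power 79% at 300 per group), not of a paired pre/post test.

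**2. Whether pairs exist for the indicators.** From Data Collection Procedure, Secondary Outcomes and Results:

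- KAP questionnaire: given at baseline and repeated at the end, so pairs exist.
- Malaria indicators: recorded monthly during the intervention, with no earlier recording described.
- Fombap: CHWs selected in August 2019, caregivers trained and kits handed out in November 2019, home treatment from December 2019. Home-tested and home-treated cases could not have entered the intervention register before then.
- At least one indicator, confirmed cases that received artesunate-amodiaquine, has cases as its denominator. A child with no confirmed case in a period has no value for that period.

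**3. What a within-area change measures.** The expected pre/post change in one area is the sum of season and secular trend, any effect of repeat questioning, and the effect of the strategy relative to that area's own starting state. A between-group comparison over the same months removes whatever is common to both areas. A within-area test removes none of it.

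**4. Illustration on paired scores.** Assumptions: 203 pairs (the enrolled Fombap caregivers), a shift of δ SD of the paired differences that is the same in both areas, and no difference between strategies. None of the δ values comes from the document. By normal approximation, P(significant) = Φ(δ√203 − 1.96) + Φ(−δ√203 − 1.96), with √203 = 14.25.

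- δ = 0: 5%.
- δ = 0.1: 0.1 × 14.25 = 1.42; Φ(−0.54) ≈ 30%.
- δ = 0.2: 0.2 × 14.25 = 2.85; Φ(0.89) ≈ 81%, or about 80% allowing for the signed-rank test's roughly 95% efficiency.
- δ = 0.2 with 15% nonresponse: 203 × 0.85 ≈ 173 pairs; 0.2 × √173 = 2.63; Φ(0.67) ≈ 75%.

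**5. Illustration on a binary indicator, as if baseline values existed.** Simulation of 2,000 studies with 300 children per area, an assumed starting rate of 0.44, independent pre and post values, the same fall in both areas and no strategy difference. On binary pairs the signed-rank test reduces to the McNemar z.

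- Fall of 0, 5, 8 or 11 points: the within-area test is significant in about 5%, 22%, 53% and 80% of studies.
- The between-group chi-square test stays at about 5% to 6% throughout.

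**The case against.** The strongest reply is that the right comparison is already in the plan. The sentence after the Wilcoxon test provides t and chi-square tests between the groups, and the primary outcome, final evaluation and sample size are all between-group. This stands. A reader might infer that the trial has no test of its hypothesis, and the text does not support that. What is missing is a statement of which test decides.

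Second, the article is condensed. A reader might infer that no earlier indicator values exist anywhere. The article shows only that it describes none and plans no use of any. For Fombap the dates of training and kits make this a strong inference. For Baneghang, where CDI was already running, earlier CHW register entries may exist, but they would not supply Fombap pairs.

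Third, the Discussion also expects each intervention to improve home management, which is loosely a within-strategy question, and the article does not say whether the Wilcoxon test runs in one area or both. A pre/post summary could describe such a change. It still could not attribute the change to the strategy, nor answer the hypothesis in the Introduction.

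Fourth, the size depends wholly on the assumed shift. The KAP score is not among the listed outcomes, and with no shift the error rate is the nominal 5%. That limits the figures to showing direction.

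**Conclusion.** The analysis is wrong as written. It assigns a pre/post test to indicators whose described collection starts with the intervention, and it attaches the claim of effect to a contrast that cannot separate the strategy from time. Neither part depends on the illustrations.

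Their size is conditional: with a common shift and no strategy difference, a within-area test on 203 pairs is significant in about 5% to 80% of studies as the shift goes from 0 to 0.2 SD. One might infer that a positive result is almost guaranteed, but that would need a shift the document does not give. Nor does the document say that Fombap had no malaria programme before the trial, only that CDI is not implemented there. So it cannot be concluded that a change in Fombap would show superiority to no programme.

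**What to change.** Rewrite the analysis paragraph as follows:

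- Remove the pre/post Wilcoxon test as evidence of effect on the malaria indicators.
- Name the already planned between-group comparison, over the intervention period, as the test of the hypothesis, and bring the Abstract's one-way analysis of variance into line with it.
- Limit pre/post summaries to the KAP scores and present them descriptively. Any claim of an effect on KAP should rest on a between-group comparison. How that comparison uses the baseline score is a separate choice, debatable for two separately selected areas, and this point does not settle it.
- State that the malaria indicators have no pre-intervention value.

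The cost is one paragraph and no new data. The downside is the loss of a within-arm P value.

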**Methods:**

A randomized controlled trial will be conducted. CHWs have conducted a census of all households where there is at least one child younger than 5 years with their home caregivers. These children and their home caregivers have been randomly placed into the intervention or control groups among the households identified. The trial will allow malaria home-based prevention, diagnosis, and treatment of 350 children younger than 5 years old by home caregivers in the Fombap area (intervention group) where the integrated CDI strategy will not implemented. This group will be compared to the home-based malaria management component of the integrated CDI strategy in which 350 children in the same age group will be followed up by CHWs in the Baneghang area (control group). The primary outcomes will be the prevention, diagnosis, and treatment of malaria in children younger than 5 years of age by home caregivers at home. The secondary outcomes comprise the malaria follow-up indicators produced by home caregivers in the intervention group and those produced by CHWs in the control group. Both descriptive and one-way analysis of variance estimation techniques will be used to compare the mean difference in the 2 strategies.

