### The Control Group

The integrated CDI strategy is implemented in 5 health districts in the West Cameroon region, including the Penka-Michel Health District, from which our control health area, Baneghang, was randomly selected for the site of the control group. In this area, the malaria management component of the integrated CDI strategy is carried out by 9 CHWs, 6 of whom were randomly selected for the study. CHWs conducted a census in their respective zone of all the households where there is at least one child younger than 5 years and their home caregivers. After identifying the households, children younger than 5 years old and their home caregivers were randomly selected for enrollment in the study.

Usually, when there is a suspected case of malaria in the community, the patient is taken to the CHW's home. The patient is examined by the CHW to check for uncomplicated malaria. If the test is positive, the CHW conducts an RDT and administers malaria treatment; if the test is negative, the CHW refers these patients and those with severe malaria to the health care center and makes home visits to provide health education to parents.

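### The stated group comparisons make no use of the baseline caregiver questionnaire, so any comparison of knowledge, attitudes and practices carries the starting difference between two non-randomised areas and loses precision

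*Protocol article*

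**What the plan says.** **Group comparison.** The Data Management and Analysis section states: "For group comparisons, the *t* test will be used to compare means, while the chi-square test will be used to compare the proportions". The Methods part of the abstract says instead that "one-way analysis of variance estimation techniques will be used to compare the mean difference in the 2 strategies". Neither mentions a covariate, a between-group comparison of change, or a difference-in-differences.

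**Use of pre-intervention data.** The same section says that "a comparison of the pre- and postintervention data will be conducted using the Wilcoxon signed-rank test for the indicators of the malaria". This is a paired test and contains no contrast between the two strategies.

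**What is measured.** Data Collection Procedure says: "For baseline data, a pretested questionnaire was administered to home caregivers on the perception (knowledge, attitudes, and practices) of malaria", and then: "This questionnaire will be repeated at the end of the intervention". The Results section reports that baseline data are already collected. The register indicators are different: "During the intervention, a structured data collection form will be used and will contain monthly malaria follow-up indicators recorded by home caregivers". No pre-intervention value of them is described.

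**How the arms arise.** Under Study Area, the intervention arm is Fombap (Santchou district, no CDI) and the control arm is Baneghang (Penka-Michel district, CDI already running). The areas were chosen by a mix of probability and nonprobability sampling. The abstract and Study Design speak of random placement into groups, but Data Collection Procedure, Step 2, The Control Group and Results describe random selection of participants within each area. Under The Control Group, the CHW in Baneghang already "makes home visits to provide health education to parents".

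**Outcomes.** Primary and secondary outcomes are the malaria follow-up indicators. KAP is in neither list.

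**The concern.** Unadjusted tests are defensible when randomisation makes the arms alike in expectation. Here a caregiver's arm is the area the caregiver lives in, and Baneghang is the control because CDI runs there. Sampling at random within each area does not make the two areas alike. A difference in caregiver knowledge or practice before December 2019 is plausible, since one area already had CHW education visits.

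Two things are at stake for any KAP comparison. First, a two-sample test on end scores mixes the starting difference with the change brought about during the trial. Second, the variance that the baseline score explains stays in the error term, although the data to remove it are in hand. The within-group Wilcoxon test repairs neither. The article names specific tests, so this concerns a stated method rather than a detail left to a fuller plan.

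**Working it through.** **Inputs from the article.** 203 and 225 caregivers (Results); two-sided alpha 0.05, z = 1.96, and 80% power, z = 0.842 (Sample Size Calculation); p1 = 0.44, p2 = 0.33, n = 300 per group.

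**The plan's own figure.** The pooled two-proportion formula at 0.44 v 0.33 gives 306 per group (303 with unpooled variance), within about 2% of the stated 300. It is sized for a proportion and uses no baseline covariate, so it says nothing about KAP.

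**Assumptions.** The article gives no baseline-to-end correlation (rho) and no baseline difference. I take rho = 0.3, 0.5, 0.7 and a gap of 0.25 SD for illustration. All caregivers are followed and clustering is ignored.

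**Precision, KAP score in SD units.**
- Unadjusted SE = sqrt(1/203 + 1/225) = 0.0968.
- Detectable difference at 80% power = (1.96 + 0.842) × 0.0968 = 0.271 SD.
- Baseline-adjusted SE = 0.0968 × sqrt(1 − rho²), so the variance falls by the fraction rho².

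| rho | variance cut | adjusted SE | detectable difference | power at 0.271 SD |
|---|---|---|---|---|
| 0.3 | 9% | 0.092 | 0.259 | 84% |
| 0.5 | 25% | 0.084 | 0.235 | 90% |
| 0.7 | 49% | 0.069 | 0.194 | 98% |

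**Bias with no effect of strategy and a 0.25 SD starting gap.** The answer depends on how the gap behaves over time. Rejection rate = Φ(b/SE − 1.96) + Φ(−b/SE − 1.96), with b the bias. The SE of the difference in change is 0.0968 × sqrt(2(1 − rho)) = 0.115, 0.097, 0.075.

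*Case A, the gap shrinks to rho × 0.25 by the end.*
- Unadjusted end comparison: b = rho × 0.25 = 0.075, 0.125, 0.175; rejects 12%, 25%, 44%.
- Adjusted for baseline: b = 0; rejects about 5%.
- Difference in change: b = −(1 − rho) × 0.25 = −0.175, −0.125, −0.075; rejects 33%, 25%, 17%.

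*Case B, the gap stays at 0.25.*
- Unadjusted end comparison: b = 0.25, b/SE = 0.25/0.0968 = 2.58; rejects 73%.
- Adjusted for baseline: b = (1 − rho) × 0.25 = 0.175, 0.125, 0.075; rejects 47%, 32%, 19%.
- Difference in change: b = 0; rejects about 5%.

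The adjusted model beats the unadjusted test in both cases, but it is clean only in case A. The difference in change is clean only in case B. The article cannot tell us which case applies, so neither analysis should be hidden behind the other.

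**Register indicators.** With no baseline value of the indicator, baseline KAP can serve only as a proxy covariate. The article gives no strength of association between KAP and any indicator, so no gain is computed.

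**The case against.** **KAP is not an outcome.** This stands. Outcome Measures lists only follow-up indicators, and the article never says that a t test will be run on end KAP scores. That is an inference: the listed secondary indicators are proportions, and KAP is measured at both ends. The figures above therefore bear on a KAP comparison if one is made, not on the endpoint that was sized.

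**The stated outcomes.** A reader might infer that the chi-square tests on the indicators should give way to KAP-adjusted models as main analysis. The article does not support this. Nothing in it shows that KAP predicts the indicators. One of them, CHW household visits, measures CHW activity, so a caregiver covariate has no evident role there.

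**Is the starting gap a bias at all?** In part, no. If Baneghang caregivers start higher because CDI already educates them, that is an effect of the comparator. Removing it changes the question from CDI against the caregiver strategy to what was gained during the trial. A reader might infer that the unadjusted test is simply biased against the caregiver strategy. That does not follow until the target contrast is stated.

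**Adjustment is no cure.** This stands. Case B shows 32% rejection after adjustment at rho 0.5, and with one area per arm unmeasured area differences remain whatever covariates are used.

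**Adjusted models belong in a fuller plan.** This has some weight, as the article is condensed. But it does commit to named between-group tests, and those leave the collected baseline out.

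**Conclusion.** The point holds in limited form. The stated between-group tests are unadjusted, the one pre/post test is within-group, and the arms are two non-randomised areas, while a baseline and repeat KAP questionnaire is available. Any KAP comparison made as stated carries the starting area difference and forgoes a variance reduction of 9% to 49%, for an assumed rho of 0.3 to 0.7, 203 v 225 caregivers, full follow-up and no clustering. The rejection rates rest further on an assumed gap of 0.25 SD and on how that gap evolves; they illustrate and do not predict.

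Nothing quantified can be claimed for the primary and secondary indicators. Nor does the point establish that baseline adjustment would make the two areas comparable.

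**What to change.** In Data Management and Analysis:

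1. For KAP scores, specify a linear model of the end score on group and the same caregiver's baseline score in place of a two-sample t test. Report the between-group difference in change beside it with equal prominence, since the two can differ when areas are not randomised.
2. State that this contrast is incremental to the CDI already running in Baneghang, and that one area per arm leaves confounding that adjustment cannot remove.
3. For the register indicators, keep the unadjusted comparison. Add, as a supporting analysis, a regression on group plus baseline KAP and prevention practices, for child- or caregiver-level indicators only and not for CHW household visits. Claim no quantified gain.
4. Align the abstract's one-way analysis of variance with this text.

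The cost is wording and some extra analysis. No new data or participants are needed. Missing baseline scores must be handled, which the multiple imputation already stated covers.

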### Sample Size Calculation

The sample size calculation for this trial study will be based on the following formula for comparing 2 groups [19]:

where p_1_ = 0.44, p_2_ = 0.33, Z_α/2_ = Z_0.05/2_ = 1.96 (from z table or type 1 error of 5%), Z_β/2_ = z_0.20_ = 0.842 (from z table at 80%), and p = pooled prevalence = (prevalence in intervention group (p_1_) + prevalence in control group (p_2_)/2).

*n* = 300

With a 15% nonresponse rate, the sample size is rounded up to 350 children younger than 5 years being assigned to the intervention group and 350 being assigned to the control group.

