## Results

In August 2019, 6 CHWs were selected with the help of the community. From September 2019 to October 2019, 408 home caregivers with their 715 children younger than 5 years were identified in the intervention area by CHWs. Among them, 350 children younger than 5 years old and their 203 home caregivers were randomly selected and enrolled in the intervention group. In addition, CHWs identified 451 home caregivers with their 708 children younger than 5 years old. Among them, 350 children younger than 5 years old and their 225 home caregivers were randomly enrolled in the control group.

In the intervention group, 203 home caregivers were trained in November 2019 to prevent and treat malaria at home for their children younger than 5 years. Diagnostic kits (RDTs and thermometers) and treatment (artesunate-amodiaquine and paracetamol) were distributed to these home caregivers during the training. Home treatment effectively started in December 2019 and will continue until May 2020. The baseline data have already been collected and are being analyzed.

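### The named chi-square and t tests assume independent records, but children share caregivers and six CHW zones per arm, so any positive intracluster correlation makes the P values anti-conservative

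*Protocol article*

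**What the plan says.** Data Management and Analysis fixes the between-arm tests. For proportions, "the chi-square test will be used to compare the proportions of malaria home-based management indicators in the intervention and control groups". For means, "For group comparisons, the *t* test will be used to compare means". Significance is declared at P<.05.

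The sampling is described elsewhere in the article:

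- **Caregivers (Results).** "350 children younger than 5 years old and their 203 home caregivers were randomly selected and enrolled in the intervention group". In the control arm, 350 children were enrolled with 225 caregivers.
- **CHW zones (Data Collection Procedure).** Six CHWs were chosen in Fombap. For the control arm, "6 CHWs were also randomly selected from the 9 in the Baneghang health area". Each CHW listed the households in his or her own zone, and children were drawn from those lists.
- **Who acts and who records (Steps 3, 4 and 6; The Control Group).** In the intervention arm, the caregiver is trained, tests, treats and reports for her own children, while the zone's CHW educates, resupplies kits and collects the indicators. In the control arm, the CHW examines, tests, treats and records.
- **Areas (Study Area).** Each arm is one health area, and the two areas lie in different districts.

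The article mentions no ICC, design effect, mixed model, generalised estimating equation or robust standard error.

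**The concern.** Chi-square and t tests obtain their standard error by treating every record as a separate piece of information. Here siblings share the person who tests and treats them, and all enrolled children in a zone share one CHW, who delivers care or collects the data. Records within a family or zone can therefore be expected to resemble one another. If they do, the true standard error exceeds the one the tests use. The nominal 5% test then rejects too often when there is no effect, and any interval computed on the same basis is too narrow.

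At stake is a false claim that one strategy is better. The primary outcome is judged on these indicators, and the Discussion says the findings will inform public health authorities.

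**Working it through.** **1. The plan's own figure.** Inputs from Sample Size Calculation: "p_1_ = 0.44, p_2_ = 0.33", a two-sided 5% level (z = 1.96), 80% power (z = 0.842).

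n = [1.96·√(2·0.385·0.615) + 0.842·√(0.44·0.56 + 0.33·0.67)]² / 0.11² ≈ 306 per arm.

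The stated 300 is within 3% of this. The allowance for 15% nonresponse gives 300/0.85 = 353 or 300 × 1.15 = 345, both close to the stated 350. The figure therefore reproduces as a calculation for independent children, that is, with a design effect of 1.

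**2. Cluster sizes, from Results and Data Collection Procedure.**

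- Children per caregiver: 350/203 = 1.72 and 350/225 = 1.56; overall 700/428 = 1.64.
- Children per zone: 350/6 = 58.3 on average. Counts by zone are not given.

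**3. Formulas.** Design effect DE = 1 + (m − 1)·ICC. True type I error of the unadjusted test = 2·[1 − Φ(1.96/√DE)]. The documents give no ICC, so every ICC below is an assumption.

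| Clustering | m | Assumed ICC | DE | 1.96/√DE | Type I error |
|---|---|---|---|---|---|
| Caregiver only | 1.64 | 0.2 | 1.13 | 1.85 | 6.5% |
| Caregiver only | 1.64 | 0.5 | 1.32 | 1.71 | 8.8% |
| Zone, all children | 58.3 | 0.01 | 1.57 | 1.56 | 11.8% |
| Zone, all children | 58.3 | 0.02 | 2.15 | 1.34 | 18.1% |
| Zone, all children | 58.3 | 0.05 | 3.87 | 1.00 | 31.9% |
| Zone, 10 cases (illustrative) | 10 | 0.01 | 1.09 | 1.88 | 6.0% |
| Zone, 10 cases (illustrative) | 10 | 0.05 | 1.45 | 1.63 | 10.4% |

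The last two rows are for indicators whose denominator is confirmed cases, such as the proportion of confirmed cases given artesunate-amodiaquine.

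**4. Check by simulation.** With 20,000 beta-binomial replicates, p = 0.385 and 6 zones per arm, chi-square rejected in 11.7%, 18.1% and 32.5% of replicates at zone ICC 0.01, 0.02 and 0.05. A t test on the 12 zone proportions rejected in 5.0%, 5.2% and 5.3%. This simulation set variation between the two areas to zero.

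**5. What the zone-level test cannot repair.** Suppose the areas also differ, with area ICC a and zone ICC z. In units of p(1 − p), the variance of an arm mean that the zone-level test can see is v = [z + (1 − a − z)/58.3]/6. The true variance is larger by the factor r = 1 + a/v. The test then rejects with probability P(|t₁₀| > 2.228/√r).

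- a = 0.01, z = 0.01: v = 0.00447, r = 3.24, threshold 1.24, rejection 24%.
- a = 0.005, z = 0.05: v = 0.01103, r = 1.45, threshold 1.85, rejection 9%.

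Other combinations of a = 0.005 or 0.01 with z = 0.01 to 0.05 fall between these.

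**The case against.** **A statistical analysis plan may handle clustering.** A protocol article may leave detail to such a plan. But this article does not leave the tests open: it names them, and they do not fit the sampling it describes. This objection fails.

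**The size is assumed.** This stands. The larger figures depend on zone ICCs that appear nowhere in the documents, and even the direction needs a positive ICC. A reader might infer that 12% to 32% applies to every indicator. It does not. It applies only where all 350 children per arm are the denominator. Indicators based on confirmed cases have smaller clusters, and household visits by CHWs are not a child-level outcome at all.

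**The unit of analysis is partly open.** This also stands. The knowledge, attitudes and practices questionnaire goes to caregivers. If the t test compares those scores, sibling clustering drops out and only zone clustering remains. Indicators are recorded monthly, so one might infer that repeated child-months are analysed as independent rows, but no section says so.

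**Area confounding is the larger problem.** With one health area per arm, no analysis of zones or caregivers can separate strategy from place. That is true and limits what the fix achieves. It does not excuse overstating precision within areas as well.

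**Abstract against Methods.** The abstract says "one-way analysis of variance estimation techniques will be used to compare the mean difference in the 2 strategies", and a reader might count this as a second error. With two groups, one-way ANOVA and the equal-variance t test are the same test, so the difference in name is no part of the error.

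**Conclusion.** The between-arm tests are wrong as written for the sampling the article describes. Given any positive ICC within caregivers or zones, which is to be expected where one person delivers or records care for the whole cluster, P values and any intervals on the same basis are anti-conservative.

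The documents do not fix the size. For the assumed ICCs shown, it runs from a modest excess over 5% (caregiver clustering alone, or zones with few cases) to a severe one (zone clustering with all children as denominator). Zones matter more than families, because about 58 children share a CHW while fewer than two share a caregiver.

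It would be tempting to conclude that a cluster-aware test restores a valid test of the strategy. The documents do not support that. Each arm is one area, and with an assumed area ICC of 0.005 to 0.01 the zone-level t test still rejects about 9% to 24% of the time under no effect.

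**What to change.** Replace the between-arm chi-square and t tests in Data Management and Analysis with one cluster-aware method, chosen before the outcome data are compared:

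- **Simpler option.** A t test on the 12 zone-level summaries, with 10 df (critical value 2.23 in place of 1.96). It gives a difference in proportions with its interval. It also absorbs sibling correlation, provided each family lies within one zone.
- **Model option.** A mixed model (logistic for proportions, linear for scores) with random intercepts for zone and caregiver and small-sample degrees of freedom. The logistic form yields odds ratios, so a risk difference needs a stated conversion step.

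State the denominator and unit of analysis for each indicator, and name the same method in the abstract. State also that the method corrects within-area clustering only: area differences remain confounded with treatment, and the P value cannot be read as a valid randomised test of the strategy.

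**Cost.** Wording and modest programming. Zone and caregiver were known at enrolment because children were drawn from zone lists of caregivers, but the article does not say that the registers carry these identifiers, so the link should be checked.

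The statistical price is wider intervals and lower power. For 0.44 against 0.33 with 350 per arm, power is 85% if children are independent. For the 10-df test, the standard error is √[DE·(0.44·0.56 + 0.33·0.67)/350] = 0.046, 0.054 and 0.072 at assumed zone ICC 0.01, 0.02 and 0.05, and power is about 58%, 46% and 28%. That loss comes mainly from the design; the present tests conceal it.
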